## Abstract

**Background:**

As of May 2022, Ontario has seen more than 1.3 million cases of COVID-19. While the majority of individuals will recover from infection within 4 weeks, a significant subset experience persistent and often debilitating symptoms, known as “post-COVID syndrome” or “Long COVID.” Those with Long COVID experience a wide array of symptoms, with variable severity, including fatigue, cognitive impairment, and shortness of breath. Further, the prevalence and duration of Long COVID is not clear, nor is there evidence on the best course of rehabilitation for individuals to return to their desired level of function. Previous work with chronic conditions has suggested that the addition of electronic case management (ECM) may help to improve outcomes. These platforms provide enhanced connection with care providers, detailed symptom tracking and goal setting, and access to relevant resources. In this study, our primary aim is to determine if the addition of ECM with health coaching improves Long COVID outcomes at 3 months compared to health coaching alone.

**Methods:**

The trial is an open-label, single-site, randomized controlled trial of ECM with health coaching (ECM+) compared to health coaching alone (HC). Both groups will continue to receive usual care. Participants will be randomized equally to receive health coaching (± ECM) for a period of 8 weeks and a 12-week follow-up. Our primary outcome is the WHO Disability Assessment Scale (WHODAS), 36-item self-report total score. Participants will also complete measures of cognition, fatigue, breathlessness, and mental health. Participants and care providers will be asked to complete a brief qualitative interview at the end of the study to evaluate acceptability and implementation of the intervention.

**Discussion:**

There is currently little evidence about the optimal treatment of Long COVID patients or the use of digital health platforms in this population. The results of this trial could result in rapid, scalable, and personalized care for people with Long COVID which will decrease morbidity after an acute infection. Results from this study will also inform decision making in Long COVID and treatment guidelines at provincial and national levels.

**Trial registration:**

ClinicalTrials.gov NCT05019963. Registered on 25 August 2021.

## Administrative information

Note: The numbers in curly brackets in this protocol refer to Standard Protocol Items: Recommendations for Interventional Trials (SPIRIT) checklist item numbers. The order of the items has been modified to group similar items (see http://www.equator-network.org/reporting-guidelines/spirit-2013-statement-defining-standardprotocol-items-for-clinical-trials/).

## Introduction

### Background and rationale {6a}

In March 2020, the World Health Organization (WHO) declared the novel coronavirus (COVID-19) a global pandemic. At the time of writing this protocol in February 2022, Ontario had confirmed more than 628,000 cases of SARS-CoV-2 since testing began. Most recently, estimates in May 2022 show this number has climbed to 1.3 million cases [1]. For most of these patients, symptoms resolve within 4 weeks of onset. However, it is becoming apparent that a significant subset of infected patients are experiencing symptoms that persist long after the typical course of acute viral infection. These individuals experience a wide constellation of symptoms, with variable intensity over time and often varying from initial acute presentation [2–6]. Currently, the prevalence and duration is not clear, nor is there evidence on the best course of rehabilitation for individuals to return to their desired level of function.

#### What is post-COVID syndrome?

The National Institute for Healthcare and Excellence (NICE) defines two distinct groups: ongoing symptomatic COVID (symptoms for 4–12 weeks) and post-COVID syndrome, which describes those with ongoing symptoms, not better explained by another diagnosis, for 12 weeks or longer [7]. The most common symptom experienced is persistent fatigue, followed by dyspnea, cognitive issues such as “brain fog” and cardiothoracic issues [2, 5, 6, 8]. Other symptoms include headaches, muscle and joint pain, persistent cough, and psychiatric conditions [2, 6, 8, 9]. An early study found that nearly half of the sample had also experienced a decrease in their quality of life [6]. It is unclear who is most at risk for developing post-COVID syndrome. While severe illness or long time to acute recovery is predictably associated with poor long-term outcomes, more than 35% of individuals with mild illness failed to return to baseline health status [10]. Women [2, 4] and ethnic minorities [11] may also be at higher risk. Previous research from the SARS pandemic also suggests that social disadvantage, such as job loss or social stigma, were also risk factors for long-term symptoms [12]. The heterogeneous nature of symptoms and risk factors suggest that an “organ-based” or classification approach will not provide optimal outcomes for these patients. An integrated model for rehabilitation, including interdisciplinary care, enhanced case management, and screening tools, should be examined [13, 14].

##### Nomenclature

There are at least four terms employed to describe persistent COVID symptoms, including “Long COVID,” “COVID-19 syndrome,” “post COVID-19 syndrome,” or “post-acute sequelae of SARS-CoV-2 infection” [2]. We have chosen to refer to the condition as Long COVID as this seems to be the term most preferred by patients [15].

#### Case management in COVID-19 rehabilitation

Previous work with chronic conditions has suggested that using digital health platforms can improve outcomes [16, 17]. These platforms usually have a patient facing app and a clinician facing dashboard and allow personalization of information and resources to the user; the tracking of symptoms, often assisted by the smartphone’s biometric sensors; contain educational resources; allow for goal setting and monitoring; facilitate collaborative care; and, create a connection between the patient and their clinician [18]. Although the size of the effect varies by condition and intervention [16, 17], these platforms are often low burden to disseminate and adaptable to individual schedules and may increase access to specialized care to patients across rural and remote regions.

Despite the explosion in e-health and coaching platforms available, a recent systematic review found there were few high-quality trials examining the effectiveness of the intervention or its individual components [19]. These platforms have been used across multiple disorders including diabetes [20–22], mental health [23–25], and cancer recovery [26, 27]. These e-health platforms also offer the opportunity for improved communication between the patient, caregivers, and care providers, increasing both understanding of and adherence to treatment protocols [18, 25, 28, 29]. In the case of Long COVID, the addition of a case management platform may prove particularly beneficial. As information is changing rapidly, patients may have more questions about their health concerns and their treatment plan. With electronic case management, clinicians can readily push new resources and information to patients and offer caregivers a more meaningful role.

#### Rationale

The most comprehensive relevant guideline regarding Long COVID is the NICE “COVID-19 rapid guideline; managing the long-term effects of COVID-19” published in December 2020 [7]. The guideline made key recommendations for research including “What is the clinical effectiveness of different service models of multimodality/multidisciplinary post-COVID-19 syndrome rehabilitation in improving patient-reported outcomes (such as quality of life).” The NICE guideline also recommended that patients use symptom diaries or a tracking app to monitor their goals, recovery, and any changes in their symptoms. This proposal directly addresses this recommendation, as the NICE guidelines provide no research to support this approach [7]. We aim to utilize these recommendations to evaluate what possible service models incorporating electronic case management (ECM) will improve outcomes in this population.

## Objectives {7}

### Primary objective

The primary objective of this trial is to determine if adding ECM with health coaching to usual care improves participant quality of life after 3 months for patients who present to hospital outpatient clinics experiencing Long COVID.

We hypothesize that adding ECM with health coaching to usual care will improve outcomes at 3 months compared to usual care alone.

### Secondary objectives

The key secondary objectives of this study are to determine (1) the cost-effectiveness of adding ECM to usual care for Long COVID patients; (2) what factors predict outcomes at 3 months in patients with Long COVID; (3) if the addition of ECM affects Long COVID symptoms; and (4) how a personalized rehabilitation program supported by a digital platform could be implemented for individuals with Long COVID.

We hypothesize that adding ECM to usual care will be cost-effective from a public-payer’s perspective. We also hypothesize that people with Long COVID who had severe acute COVID infections, adverse childhood experiences, recent negative life events, or a strong sense of injustice at baseline will have poorer outcomes at 3 months. Lastly, we hypothesize that those with ECM will show more improvement across outcome measures at 12 weeks.

Following the Medical Research Council guidance on developing and evaluating complex interventions [30], we will conduct a process evaluation guided by the RE-AIM implementation framework [31].

## Trial design {8}

The proposed study is a 12-month open-label, parallel group, randomized controlled trial. Participants will be allocated 1:1 into either electronic case management (ECM+) with health coaching plus usual care or health coaching plus usual care alone (HC). Due to the nature of the intervention, it will not be possible to blind clinicians or patients to the allocation.

## Methods: participants, interventions, and outcomes

### Study setting {9}

This single-site study will be conducted at the Ottawa Hospital Research Institute (OHRI). Recruitment will occur through two different streams to increase the diversity of participants. The first stream is a clinic that sees Ontario workers who were infected by SARS-CoV-2 at their worksite, who have made a claim to the Ontario Workplace Safety and Insurance Board (WSIB) and are assessed by the Ontario Workers Network (OWN) based at The Ottawa Hospital (TOH). The second stream are clinics within TOH which are seeing patients with Long COVID. These are clinics specifically for people with Long COVID, for example within the rehabilitation service, or specialist clinics that are seeing people with Long COVID such as respirology, infectious diseases, or psychiatry.

### Eligibility criteria {10}

Participants will be recruited from TOH. Participants will be approached by an individual in their circle of care if they meet the eligibility criteria outlined in Table 1.

**Table 1 Tab1:** Eligibility criteria

Inclusion criteria	
Participants must:	
1.	Be 18 years of age or older
2.	Have a confirmed diagnosis of COVID-19 with a PCR test at least 12 weeks prior OR a confirmed rapid antigen test at least 12 weeks prior OR meet Ottawa Public Health guidance for a suspected COVID-19 case (Table 2)
3.	Have at least one ongoing symptom consistent with Long COVID as measured by the WHO Post COVID Case Report Form (CRF)
4.	Have a minimum WHO Disability Assessment Scale (WHODAS) self-report (36 item) sum score of 15
5.	Be willing to use email for study activities
6.	Be able and willing to use an electronic platform, either on smartphone or computer web browser, for the duration of the trial
7.	Be able to read and understand English or French.
8.	Be willing and able to provide informed consent.
Exclusion criteria	
Participants must not:	
1.	Have any significant functional impairment (for example, advanced dementia, heart or lung disease) as judged by the assessing clinician
2.	Participate in another Long COVID trial where treatment is required in the protocol (pharmacological or behavioral). Observational studies will be allowed.
3.	Have symptoms consistent with Long COVID that are better explained by an alternative diagnosis

#### COVID-19 testing eligibility

Effective December 30, 2021, the government of Ontario significantly restricted the eligibility for PCR testing. The general public is no longer eligible for symptomatic PCR testing (https://news.ontario.ca/en/backgrounder/1001387/updated-eligibility-for-pcr-testing-and-case-and-contact-management-guidance-in-ontario). Rapid Antigen Tests (RAT) are also significantly limited in Ontario and these results are not officially reported to any health agency. Additionally, in early 2020, testing was unavailable or highly limited. A previously approved, but not implemented, version of this protocol limited eligibility to PCR test only. To ensure that we are able to enroll individuals, inclusion criteria for testing will not be limited to PCR. The preferred confirmation of eligibility will remain a PCR test 12 weeks prior. Second line of eligibility confirmation will be a positive RAT 12 weeks prior. Third line will be for the participant to confirm a suspected case of COVID-19 indicating they were experiencing symptoms at least 12 weeks prior. Determination of a suspected case will follow the Ottawa Public Health Guidelines (https://www.ottawapublichealth.ca/en/public-health-topics/resources/Documents/Self-Isolation-Flowchart_EN.pdf) summarized in Table 2.

**Table 2 Tab2:** Suspected COVID-19 eligibility criteria

If you experienced one of:	If you experienced two or more of:
Fever/chills Cough Shortness of breath Decrease/loss of smell or taste	Sore throat Headache Runny nose/nasal congestion Extreme fatigue Muscle/joint pains GI symptoms (vomiting, diarrhea)

Potential participants will be asked to confirm that symptoms were a minimum of 12 weeks ago, and the delegated research staff will document the date and the list of symptoms experienced. The Principal Investigator will then make the final determination about inclusion in the study.

#### Access to technology

Participants are not required to have a smartphone with a data plan in order to participate in the intervention arm. Participants will be able to access their patient dashboard from their computer or tablet with internet access. Participants who do not have any available options to access the platform and are randomized to the intervention arm will be provided with one pre-paid smartphone with voice and data services for the duration of their study participation. Provision of a second phone in the event of loss or theft will be evaluated on a case-by-case basis.

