### Strategies to improve adherence to interventions {11c}

No particular strategy will be implemented to improve adherence to the intervention as this is an outcome of the study. As part of the process evaluation, we are examining factors affecting adherence to the intervention. We will evaluate any differences in adherence between the treatment and intervention groups.

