### Participant timeline {13}

Administration will occur as per the Time and Events Schedule in Table 5. Clinical visits will occur as needed and will be determined during the initial assessment. Clinical visits are not outlined in the time and event schedule as these are a part of routine care. Self-report measures will be completed at home prior to each study visit using the study Electronic Data Capture System (EDCS). Participants will be able to leave and return to the questionnaires whenever they need to complete them. It is anticipated the first and last visit will take approximately 45 min, while weeks 4 and 8 will take approximately 30 min. Participants will complete the WHODAS first and all responses are mandatory. All other self-report measures will be completed in a structured order.

**Table 5 Tab5:** Time and events schedule

Measures	Time to complete (minutes)	Administration	Baseline	Week 4	Week 8	Week 12
WHO Post COVID CRF Module 1	Variable	Chart review	**X**			
WHO Post COVID CRF Module 2	Variable	Chart review	**X**			**X**
WHO Post COVID CRF Module 3	Variable	Chart review	**X**			**X**
Demographics	<5	Self-report	**X**			
ACE-Q	5	Self-report	**X**			
Injustice Experience Questionnaire (IEQ-SF)	<5	Self-report	**X**			
WHODAS	5	Self-report	**X**	**X**	**X**	**X**
PHQ-9	<5	Self-report	**X**	**X**	**X**	**X**
GAD-7	<5	Self-report	**X**	**X**	**X**	**X**
PCL-5	5	Self-report	**X**	**X**	**X**	**X**
EQ-5D-5L	<5	Self-report	**X**	**X**	**X**	**X**
AUDIT	<5	Self-report	**X**			**X**
ASSIST	5-10	Interview	**X**			**X**
Fatigue Severity Scale	<5	Self-report	**X**	**X**	**X**	**X**
PSQI	5	Self-report	**X**	**X**	**X**	**X**
Warwick-Edinburgh Mental Wellbeing Scale (WEMWBS)	5	Self-report	**X**			**X**
Pain Numeric Rating Scale	<5	Self-report	**X**	**X**	**X**	**X**
MRC Dyspnoea Scale	<5	Self-report	**X**	**X**	**X**	**X**
Cognition (Trailmaking, Hopkins Verbal Learning, Digit Span, Phonemic/Semantic Verbal Fluency)	30	Interview	**X**			**X**
Qualitative Interview (Optional)	30	Interview				**X**

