## Data collection and management

### Plans for assessment and collection of outcomes {18a}

All self-reported outcome measures will be administered via the EDCS for all study visits. Interview measures, when done remotely, will be completed using a videoconferencing platform. Information from the WHO Post-COVID Assessment CRF will be entered by delegated study staff into the EDCS.

Cognitive assessments will be administered by a trained research staff member. The delegated study staff member will receive direct training from an experienced Psychologist, including rehearsal and independent evaluation, prior to administration with participants.

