### Plans to promote participant retention and complete follow-up {18b}

A major difficulty in all clinical research is ensuring participants attend their visits and stay enrolled in the study. Efforts will be made to minimize the time between being approached about the study and the baseline visit. We anticipate lost to follow-up to be no more than 20%. While there is currently no available literature on the lost to follow-up rates for Long COVID rehabilitation, the case management platform we are using has demonstrated significantly higher levels of retention in difficult to treat populations [24]. For those participants in the intervention arm, daily and weekly reminders will be programmed into the NexJ Connected Wellness platform to encourage regular use and increase connectedness with the platform, increasing retention.

We will implement an escalated approach if contact is lost with individuals between study visits. The appropriate response will be determined in collaboration with the Principal Investigator, particularly if there is a potential safety concern. If contact is made with the participant and they are no longer interested in participating, the delegated study staff member will make every effort to ascertain why they are withdrawing their consent. Participants will be sent the link to complete their self-report questionnaires at each time point unless they have withdrawn their consent for participation.

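### Device support goes only to ECM+ although both arms report the primary outcome online, and ECM+-only NexJ reminders are counted as a retention measure

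*Protocol article*

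**What the plan says.** **Device.** The Access to technology section foresees participants with no means of access. Those who lack any option "and are randomized to the intervention arm will be provided with one pre-paid smartphone with voice and data services". Nothing comparable is stated for HC. Eligibility criterion 6 asks that people be able and willing to use an electronic platform; it does not ask that they own a device.

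**Outcome collection.** The rule is the same for both arms. Section {18a} states that "All self-reported outcome measures will be administered via the EDCS for all study visits", and section {13} states that "Self-report measures will be completed at home prior to each study visit", in the electronic data capture system (EDCS). Section {19} describes that system as web-based. The WHODAS is due at baseline and weeks 4, 8 and 12.

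**Retention.** Section {18b} says: "For those participants in the intervention arm, daily and weekly reminders will be programmed into the NexJ Connected Wellness platform to encourage regular use". The purpose given is to "increase connectedness with the platform, increasing retention". The same section expects loss of no more than 20%, without a split by arm, and supports this by saying that "the case management platform we are using has demonstrated significantly higher levels of retention in difficult to treat populations". It also sends the questionnaire link to everyone who has not withdrawn consent, and provides escalated contact when a participant is lost between visits.

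**Adherence.** Section {11c} says: "No particular strategy will be implemented to improve adherence to the intervention as this is an outcome of the study". It also plans to compare adherence between the groups.

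**The concern.** Whether a participant can supply the primary outcome should not depend on allocation. For people without a device it does, as the article is written: the phone that lets an ECM+ participant use NexJ also lets that person open the questionnaires, and the matching HC participant gets nothing. The retention section points the same way, because it counts an ECM+-only feature as a means of keeping people in the trial.

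At stake is missing primary-outcome data that depends on arm, in an open-label trial with a self-reported endpoint. People without a device may differ in disability or socioeconomic position, so the week-12 respondents could differ between arms for reasons unrelated to the effect of ECM. The EQ-5D-5L responses behind the QALYs come by the same route. Separately, if NexJ use is prompted daily and weekly, usage data cannot be read as unprompted adherence.

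**Working it through.** **1. Access route by arm, as written.**

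| | Has a device | Has no device |
|---|---|---|
| ECM+ | own device | pre-paid phone with data |
| HC | own device | none stated |

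The EDCS needs a web connection at home in all four cells. Only the lower right cell has no stated route.

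**2. The plan's loss figure.** Section {14} takes 63 per arm and allows 20%: 63 × 1.2 = 75.6, rounded up to 76 per arm and 152 in total. Section {18b} repeats the 20%. One figure serves both arms, while the evidence offered for it concerns a platform that only one arm receives. The target difference is 10% of a mean of 17, which is 1.7 points, with SD 4. (Two separate matters do not affect this point: dividing by 0.8 gives 126 / 0.8 = 157.5, so 158 rather than 152; and 63 per arm matches a difference of 2.0 points rather than 1.7.)

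**3. Unequal loss, illustration.** The documents give no loss by arm, so the splits are assumed, each averaging 20%. Let g be the mean of those lost minus the mean of completers, assumed equal in both arms. Each completer mean lies below its full-arm mean by loss × g, so

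shift in the contrast = (loss in HC − loss in ECM+) × g.

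| Loss ECM+ / HC | g = 2 points (0.5 SD) | g = 4 points (1 SD) | Share of 1.7 |
|---|---|---|---|
| 15% / 25% | 0.10 × 2 = 0.2 | 0.10 × 4 = 0.4 | 12% to 24% |
| 10% / 30% | 0.20 × 2 = 0.4 | 0.20 × 4 = 0.8 | 24% to 47% |
| 5% / 35% | 0.30 × 2 = 0.6 | 0.30 × 4 = 1.2 | 35% to 71% |

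**4. Device gap alone, illustration.** Assume that 5% to 10% have no device (0.05 × 76 = 3.8 to 0.10 × 76 = 7.6, so about 4 to 8 per arm), that all of them are lost in HC and none in ECM+, and that they score 4 points worse than the others. The HC mean then shifts by 0.05 × 4 = 0.2 to 0.10 × 4 = 0.4 points. These losses may already sit inside the HC percentages in step 3, so the two results must not be added.

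**5. Direction.** Higher WHODAS means more disability. If those lost from HC are worse off, the remaining HC participants look better and a benefit of ECM+ is masked. If those lost are better off, the sign reverses.

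**6. Power.** With 76 per arm before loss, SE = 4 × √(1/n₁ + 1/n₂) and power = Φ(1.7/SE − 1.96). At 20/20 (60.8 and 60.8 remaining) this is 64.9%; at 5/35 (72.2 and 49.4) it is 63.4%. Unequal loss at the same average costs about 1.5 percentage points of power. The risk is bias.

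**7. What the planned analysis removes.** Steps 3 and 4 are raw completer shifts. Section {20c} imputes outcomes (10 data sets) when more than about 5% are missing, which every split in step 3 exceeds on average. Imputation reduces the shift only as far as recorded variables explain the loss. Baseline WHODAS, income, education and housing are collected; device access is not listed in Table 4.

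**8. Adherence text.** Section {11c} rules out a strategy to improve adherence because adherence is an outcome. Section {18b} programs reminders intended to encourage use of the platform. Both cannot stand as written.

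**The case against.** A reader might infer that every means of staying in the trial and reporting outcomes goes to ECM+ alone, and that loss therefore differs between arms by design. The article does not support that. The questionnaire link and escalated contact are not restricted by arm (section {18b}), nor is staff follow-up of missing entries (section {19}). All participants may have coaching up to once a week (Timing of sessions).

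The affected group is also narrow. Criteria 5 and 6 require willingness to use email and ability to use an electronic platform. The eligibility threshold means that each person has supplied a WHODAS once before randomization, although the mode is not stated. NexJ reminders are partly intervention content: the description of the experimental arm mentions reminders for medication adherence, and section {18b} ties the daily and weekly prompts to platform use, not to the WHODAS. Better retention under ECM+ could itself be an effect of the intervention. The bias figures rest on assumptions and describe completer means, whereas the plan is intention-to-treat with multiple imputation. Finally, a journal article may leave backup completion modes to the full protocol.

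Most of this stands and limits the size of the point. It does not remove it. The device provision is not a matter of silence: the article states it and restricts it by arm. Shared links and contact do not help someone who cannot open the questionnaire at home. And it is section {18b}, not the reader, that presents the NexJ prompts as a retention measure.

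**Conclusion.** The point holds in a limited form. As written, an HC participant without a device has no stated way to report the primary outcome, while the ECM+ counterpart has one. Loss may be expected to be lower in ECM+, because the retention section says that the platform and its reminders raise retention and rests its common 20% on that. This is an expectation about direction; neither the text nor the figures establish that loss will differ.

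The number affected and the size of any bias cannot be derived from the article. The 0.2 to 1.2 points in the unequal-loss table follow from assumed loss splits and an assumed 2- to 4-point gap, before imputation, and should not be quoted as estimates. The number without a device is probably small. Nor do the documents support reading the gap as a source of false benefit: if those lost from HC are worse off, it would hide benefit. The conflict between sections {11c} and {18b} is a matter of wording that affects how adherence is interpreted, and is not evidence of unequal loss.

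**What to change.** 1. In Access to technology, offer support for completing outcomes to any participant without access, whatever the allocation: a loan device, or completion by telephone or on a clinic device at the study visits already scheduled.
2. In section {18b}, send identical questionnaire reminders from the EDCS to both arms on the same schedule, and do not rely on NexJ prompts as the trial's retention measure.
3. Reconcile sections {11c} and {18b}: describe NexJ reminders as a component of the intervention, and interpret NexJ usage as prompted usage.

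The cost is a few loan devices or some staff time at visits, plus automated emails. The one drawback is a mixed completion mode for a few participants, under a rule that is the same in both arms. The NexJ intervention itself is unchanged.
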